**Table 2 Tab2:** **Research evaluation procedures and timeline**

**Months after enrollment in FES**	**0**	**6**	**12**
SIPS	x		
SOS & Prescription Medication Log	x*		
Pathways to Care Interview	x		
SCID I, selected SCID II sections	x		x
Demographics, Medical History	x		
Neurocognitive & Social cognitive battery:	x	x	x
1. premorbid IQ estimate- WRAT-4 reading (*only at baseline)*			
2. processing speed: MATRICS symbol digit			
3. verbal learning: MATRICS Hopkins verbal learning test			
4. social cognition: MATRICS- MSCEIT			
Habits inventory, AUS/DUS, Cannabis Scale	x	x	x
PANSS, Calgary Depression	x	x	x
Premorbid Adjustment Scale	x		
Global Functioning: Social and Role	x	x	x
Service Utilization and Resources Form (modified)	x	x	x
Service Engagement Scale (SES)		x	x
LUNSERS medication side effect scale	x	x	x
GAF, Heinrichs QOL, SF-36 Health Survey	x	x	x
Suicidality (C-SSRS), Aggression (MOAS)	x	x	x

**repeated within one month if confidence in DUP estimate is “possible” or “probable”.*

Raters at each site will be trained using a set of common vignettes developed from historical cases at each site. Reliability assessment will focus on accurate measurement of DUP and pathways to care. Regular consensus calls will determine the team’s level of confidence (definite, probable or possible) in psychosis onset date from the SOS and offset date from the Prescription Medication Log. These measures will be repeated at 1 month when confidence in the initial estimate of DUP is only “possible” or “probable”. Ongoing monitoring of inter-rater reliability, as often as every three months for the key measures, will help reduce drift among raters and between sites.

### Statistical considerations

#### Choice of primary and secondary outcomes

The primary outcome of this study is DUP2. This is related to our primary aim of shortening time to entry into an FES with established effectiveness. We consider DUP1 a more direct measure of the ‘demand’ contributors to overall DUP, while the difference (DUP2-DUP1) related more directly to ‘supply’ side contributors.

The secondary aim of this study is to determine if DUP reduction results in improvements in clinical state at enrollment and improvements in treatment engagement and functional outcomes above and beyond that afforded by an FES. There is no evidence of a threshold at which DUP becomes significantly more determinative of outcome [68]. Analyses from different cohorts have suggested that efforts be made to shorten DUP to <1 month [69] or <3 months [70] but these differences likely result from heterogeneity in the samples and nature of the outreach efforts. Given this, we will not use an arbitrary threshold to adjust for baseline DUP (that could post-hoc make our FES’ look better or worse), but instead used linear regression across the full range of baseline DUPs to interrogate mediation effects on differential outcomes across the 2 sites.

#### Sample size and power

Since there is no conventional closed-form to estimate the statistical power for this type of design, we applied a flexible method to simulate the power empirically [71]. 1000 simulation datasets were generated by drawing random examples based on the alternative hypothesis of the design. The proposed analysis was then performed in each simulated dataset. The empirical power is the fraction of p values which are smaller than 0.05.

Extant measures of DUP are known to have a non-normal distribution, and the natural log-transformation will be used to estimate sample size. Our primary hypothesis is that the ED campaign will effectively decrease DUP at STEP vs. PREP (non-ED site). Based on historical data from 2006–2013, the estimated geometric means and standard deviations were 3.7 ± 3.7 months (corresponding to 1.3 ± 1.3 in a natural log scale) for PREP and 5.0 ± 3.7 months (corresponding to 1.6 ± 1.3 in natural-log scale) for STEP. We project that DUP will remain within the same range at PREP during years 2 through 4, but will decrease from 1.6 to 0.8 in the natural log scale at STEP (ED site). This effect size corresponds to a 55% decrease in the geometric mean DUP (months), and is comparable to the TIPS I study (1997–2000, n = 281) that reduced DUP to a median of 5 weeks [range, 0–1196 weeks] from 16 weeks [range, 0–966 weeks]. To power our study, we include historical DUP data from PREP (n = 44) and STEP (n-99) into the pre-campaign group. We plan to enroll 22 more subjects at PREP and 34 more at STEP during the first year (pre-campaign, as the baseline control for each site), as well as 66 participating at PREP and 102 participants at STEP during years 2, 3, and 4 (post-campaign). With the sample sizes of 66 (44 plus 22) at PREP and 133 (99 plus 34) subjects at STEP during the pre-campaign period, and 66 at PREP and 102 at STEP during the post campaign period, we will have 81% empirical power to detect a difference of 0.8 in the change of log-DUP from pre to post period between two sites at 0.05 alpha level.

#### Analysis plan

Patient characteristics will be compared between sites and between periods. The primary analysis will be two-way analysis of variance (two-way ANOVA) that includes two categorical explanatory variables both with two levels: period (“pre campaign” & “post campaign”) and site (“STEP” & “PREP^R^”). The combination of historical data since 2006 and the first year outcome data for each site will serve as the reference to estimate change in DUP (in natural log scale) at each site. The primary hypothesis is the ED campaign will result in greater decline in DUP at STEP compared to PREP^R^. The interaction of period and site will be used to test this hypothesis. This test is of primary interest for our study, although linear contrasts will be also conducted to compare between-site differences for the pre- and post-campaign periods. A significant interaction effect between period and site will disconfirm the null hypothesis and show that the outcome varies between pre and post campaign periods depending upon the employment of early detection. We do not anticipate significant main effects, but a significant study period effect would indicate a pre vs. post study difference on average across sites and a significant site effect would indicate that one site had a greater DUP on average across study periods. In addition, adjusted analyses will be performed with inclusion of covariates. Potential confounders such as participants’ age, gender, race/ethnicity will be included in the adjusted analyses.

A supportive analysis will investigate any effect of time by including the fixed effect of year. Other secondary analyses will include modeling of the observed percentiles of DUP (e.g., quartiles in months) using quantile regression, with the same main and interaction effects as in the approach of primary analysis. Overall, we chose our primary analysis to reflect an investigation of perhaps the most clinically meaningful change in DUP (decrease from pre period at STEP), whereas our supportive analysis will give us more insight into how early detection affects DUP across the range of DUPs observed during the pre period.

Other analyses related to our secondary aim, will interrogate whether and to what extent DUP reductions predicted improvements in clinical presentation, treatment engagement and measures of symptomatic and functional recovery.

Statistical significance will be established in all analyses at alpha = 0.05 and analyses will be performed using SAS 9.3 (Cary, NC).

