We integrate these ideas in a modified version of the influential Goldberg-Huxley model [34] (Figure 1) to understand the interaction of both patient/caregiver factors and system factors relevant to DUP. The choices for sampling, ED implementation, measurement and analysis, described in the succeeding sections, derive from this model. While not exhaustive, the boxes correspond to the most common ‘levels’ or recognized sources of care in STEP’s target catchment (8 towns). The model conceives of these levels as not just sources of referral or delay but rather as ‘filters,’ hastening access to STEP for some kinds of patients while potentially delaying it for others. This phenomenon of filtering, whereby different levels of care may influence access in non-random ways, is exemplified by STEP’s experience of rapid (short-DUP) referrals of agitated, predominantly male patients from acute settings on the one hand, while also explaining a paradoxical finding reported in other settings: prior connection to outpatient care may actually delay entry to specialty FES [35]. Particular kinds of patients may proceed through particular ‘levels’ of care with unexpected speed or delay and this suggests the need to target, measure and analyze sources of DUP within the context of local pathways.

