### Primary aim

Any test of a DUP reduction strategy in a community has to consider 2 main sources of confounding. First, unexpected changes in either direction for DUP may occur over the life of this study (e.g. variation in healthcare access due to macroeconomic changes) that will imperil inferences from the sole use of a historical control to determine the impact of ED on DUP. The parallel control in this proposal (PREP^R^) ameliorates this concern by being carried out during the same period and allowing for careful measurement (see below) of these influences. In addition, the historical control design in New Haven (pre- and post-ED) also allows us to consider the effects of ED without the impact of unknown sources of heterogeneity in DUP across sites. The second source of confounding is preferential sampling from the larger target sample of new onset cases. For example, a correlation between ED and shorter DUP might merely reflect strategic success at diverting short DUP cases to STEP, while longer DUP cases remain untreated, or treated elsewhere, in the community. This is addressed by (a) our intensive media and targeted education campaign to facilitate representative recruitment from across the catchment and (b) the availability of a historical control at the STEP site, wherein DUP distributions available for years before ED implementation will allow pre-post comparisons to assess for differential skewing. Finally, (c) DUP will also be measured at a major community mental health center (the Hill Health Center, HHC, Connecticut) in the catchment area of the ED intervention for one year before and during the ED implementation. Specifically we will measure DUP for those who are not successfully referred to STEP. Three possibilities will be considered for this group: if DUP at HHC remains the same or falls, this would reassure us that ED had no effect or a salutary effect on help-seeking, even if not to STEP; while if the DUP rises for this group, it would raise concerns for biased sampling as described above. Notably, such skewed sampling did not occur in the TIPS project [37] and given the similar catchment based design, and the reality that few competing resources for early psychosis care are available in the STEP catchment, such skewing is unlikely to occur in STEP-ED.

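### The primary site-by-period test is an unadjusted ANOVA on a non-randomised comparison; the covariate-adjusted model already planned as an extra should be primary

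*Protocol article*

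**What the plan says.** All of the primary modelling is in the protocol article, Statistical considerations, Analysis plan.

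- Primary model: "The primary analysis will be two-way analysis of variance (two-way ANOVA) that includes two categorical explanatory variables both with two levels". The two variables are period and site; no covariate is included.
- Primary test: "The interaction of period and site will be used to test this hypothesis".
- Case-mix check: "Patient characteristics will be compared between sites and between periods".
- Adjustment, outside the primary analysis: "In addition, adjusted analyses will be performed with inclusion of covariates". The covariates are given by example: "Potential confounders such as participants’ age, gender, race/ethnicity will be included in the adjusted analyses".

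Other sections show that the authors expect selective entry. The section on contextualizing early detection within pathways to care describes levels of care as filters and gives as an example STEP's experience of "rapid (short-DUP) referrals of agitated, predominantly male patients from acute settings". Under Design rationale, Primary aim, preferential sampling is named as one of two main sources of confounding. Among the planned responses are a look at STEP's DUP distributions before and after the campaign, which "will allow pre-post comparisons to assess for differential skewing", and a sentinel centre in the STEP catchment: "Specifically we will measure DUP for those who are not successfully referred to STEP".

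**The concern.** Sites were not randomised, and the campaign runs at one site only. The site-by-period interaction protects against two things: a lasting difference between the STEP and PREP populations, and a change over time common to both. It does not protect against a change in who enters that happens at one site and not at the other. Yet the campaign sets out to change the routes by which patients reach STEP, so a change of that kind is plausible.

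If the changing trait is related to DUP, the unadjusted interaction mixes the campaign's effect on DUP with the effect of a different patient mix. The article lists age, gender and race/ethnicity as potential confounders, and ties gender to short DUP in its own example, yet the test that decides the trial ignores them. This choice is stated in the article. It is not a detail left to a fuller document.

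**Working it through.** **Inputs.** From Sample size and power: SD of log-DUP 1.3 at both sites; STEP 133 before and 102 during the campaign; PREP 66 and 66; target interaction 0.8; stated power 81%. Alpha 0.05 is from the Analysis plan; two-sided testing is assumed.

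**Step 1: reproduce the plan's figure.** The interaction is a contrast of four cell means.

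SE = 1.3 × √(1/133 + 1/102 + 1/66 + 1/66) = 0.2837

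Power = Φ(0.8/0.2837 − 1.96) = Φ(0.860) = 80.5%

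This agrees with the stated 81%, so the stated power is that of the unadjusted two-sided interaction with the historical cases pooled in.

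**Step 2: what the interaction lets through.** Let a trait have prevalence p in each cell and raise log-DUP by g. Its contribution to the interaction is

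g × [(p STEP post − p STEP pre) − (p PREP post − p PREP pre)].

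A constant site difference and a common change both make the bracket zero. A differential change does not, and it is carried over in full.

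**Step 3: illustrative size.** The documents give no case-mix figures. Assume g = 0.5 and a differential shift of 20 or 30 points, with no true campaign effect. The rejection rate is P(|Z + bias/0.2837| > 1.96).

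| Differential shift | Bias | Share of 0.8 | Bias/SE | False-positive rate |
|---|---|---|---|---|
| 20 points | 0.10 | 12.5% | 0.35 | 6.4% |
| 30 points | 0.15 | 19% | 0.53 | 8.3% |

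With a stronger trait (g = 1.0) and a 20-point shift at STEP only, a simulation of 3000 runs gave a bias of about 0.20 in size and 9.8% false positives. Adding the trait as a covariate brought the bias to about 0 and the error rate to about 5%.

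**Step 4: can the planned comparisons see such a shift?** Suppose STEP goes from 50% to 70% and PREP stays at 60% (assumed).

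- Between sites, periods pooled: 58.7% v 60.0%, p = 0.81.
- Between periods, sites pooled: 53.3% v 66.1%, p = 0.013.
- Formal site-by-period test: z = 1.89, p = 0.059.

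The pooled period comparison flags the change. The formal interaction test does not reach 0.05. In the simulation of a 20-point STEP-only shift from 50%, detection rates were 36% (pooled site), 65% (pooled period), 87% (STEP before v during) and 46% (formal interaction).

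**Step 5: which age to adjust for.** Age at entry equals age at onset plus DUP2, so it contains the outcome. The resulting attenuation is small, about 2% in a simulation with assumed ages. A rerun with mean onset age 22, onset-age SD of 3 to 5 years and DUP capped at 36 months (mirroring the three-year eligibility limit) gave 1% to 2%; without the cap, 3% to 8%. Adjusting for age at onset gave no attenuation.

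**The case against.** The strongest reply is that the risk is already recognised and handled. Adjusted analyses are prespecified. The Primary aim section plans the pre-post check of DUP distributions and the sentinel centre; the Sampling section adds the prognostic profile of non-referred patients there, records exclusions and refusals, and estimates DUP in eligible refusers. The Secondary aim section says biases from refusal and exclusion will be measured and adjusted for.

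Most of this stands, and it defeats a tempting stronger reading. A reader might infer that the case-mix check looks only at pooled sites and pooled periods, so that a differential shift would go unseen into the campaign effect. The documents do not support that:

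- The sentence on patient characteristics does not say that the comparisons are pooled. It fits equally well with comparing periods within site and sites within period.
- Even pooled comparisons would often show a STEP-only shift (Step 4).
- A case that looks balanced on both margins can be built: 55% to 70% at STEP with 70% to 55% at PREP gives p = 0.85 by site and p = 0.42 by period. It needs PREP to move the opposite way, which nothing in the article suggests. Even then, STEP before v during gives p = 0.019.

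The direction of bias is also open. If the campaign opens other routes, the share of short-DUP acute entrants at STEP could fall, which would work against the campaign; diverting short-DUP cases to STEP would work for it.

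What the reply does not answer is the status of the models. The pre-post, sentinel and refuser checks look mainly at DUP, which is the outcome, so at STEP they cannot separate a campaign effect from a change in who enters. The Secondary aim text is written for another question. None of these checks alters the primary test, which remains unadjusted.

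**Conclusion.** The point holds as a matter of which model is primary. The article fixes an unadjusted interaction as the decisive test of a non-randomised comparison and leaves adjustment to additional analyses, although it names selective entry as a main threat and lists the covariates it would use. A site-specific change in case mix would enter the primary estimate in full.

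The size is modest under the illustration: 0.10 to 0.15 on the log scale, or about 0.35 to 0.53 standard errors, with a false-positive rate of 6.4% to 8.3%. These figures rest on an assumed shift of 20 to 30 points and an assumed trait effect of 0.5; neither is in the documents, and the sign is unknown. Adjustment removes only the part carried by measured, included traits. It does not cure selection on DUP itself, and gender is at best a partial proxy for the agitated, acute-setting presentation that the article describes.

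**What to change.** 1. Make the covariate-adjusted site-by-period model primary, with gender, race/ethnicity and age at psychosis onset. Use age at onset, not age at entry, because age at entry contains DUP2. Report the unadjusted ANOVA as supportive.
2. Keep the planned comparisons of characteristics. Show each characteristic in the four site-by-period cells with its difference in change as a description. Do not replace the existing comparisons by a site-by-period significance test, which is less sensitive to a STEP-only shift.
3. Do not adjust for route of entry. The campaign aims to change it, and adjustment could remove part of the effect under test.

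Cost: a change of wording, using covariates the article already names plus the onset date that DUP measurement requires. Some historical cases may lack a covariate, so the plan should state in advance whether imputation or a missing category will be used.

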## Discussion

This study will adapt and test an approach to early detection that will employ several innovations in design, delivery and measurement highlighted below:Innovating with the end in mind. The project leverages existing public-academic collaborations to implement a catchment-based approach to early detection. This will allow evaluation of scalability across similar sectors of the state and country for a given value (outcomes/cost) [72]. STEP and PREP^R^ are each integrated, within 2 of 50 nationwide State Mental Health Agencies that constitute a de facto national mental health system, reaching into nearly every community in the country and serving patients in the public sector, with serious mental illnesses. While states differ considerably in the level and mechanisms of funding, the presence of a 50 + year old infrastructure in the public sector with experience in the care of severe and persistent mental illnesses provides a natural framework within which to build a national approach [18].The use of social marketing has not to our knowledge been previously attempted for improving access to mental health care. This involves the adaptation of commercial marketing approaches towards behavior change that will be applied in the service of public health goals. A variety of stakeholders (parents, friends, professionals and young patients) whose behavior this campaign will seek to influence, will be engaged to develop and test messages. Online analytic tools will be used to track the uptake of messages and refine the campaign and represents an advance over traditional, static mass media messaging. Furthermore, the leveraging of social media to target adolescents and young adults will we hope deliver more effective and age appropriate ways to engage a population well known to resist entry into mental healthcare systems which have been traditionally oriented towards older, chronically ill patients. The details of the resulting campaign will be described in a forthcoming paper.The project takes a deliberately ‘interventionist’ stance to assessing local pathways to care i.e. the mounting of a campaign targeting presumed sources of DUP is expected to reveal more actionable information about these sources of delay and other salient features of local pathways. This is in contrast to surveying the community for barriers that may not reliably predict those that are actually operative in determining DUP. This is in keeping with our model of DUP as resulting from a more dynamic interplay between demand and supply contributors.

Pathways to care for each patient will be systematically assessed using structured interviews of patients, caregivers and clinicians and reviews of clinical documents. Barriers of greatest salience (magnitude and/or malleability) are presumed to vary across the heterogeneous U.S. landscape. Our use of a measure that will allow generation of locally detailed maps will allow us to describe and respond to the sometimes exquisitely local barriers that characterize U.S. pathways to care. While TIPS focused on enhancing mental health literacy on the one hand and making FES more rapidly responsive to referrals on the other, it took for granted the existing institutional structures that defined the pathways within which patients and caregivers sought care. By taking a more agnostic stance on pathways and assessing in detail events and actors in both the ‘demand’ and ‘supply’ sides of DUP we will be able to provide information on how these individuals and organizations perform as a network of care and suggest sustainable ways to change them and sustain DUP reductions beyond the life of the campaign.

In summary, testing an empirically based DUP reduction strategy (Primary Aim) is a logical next step for both FES programs (STEP & PREP^R^) as we seek effective ways to hasten access to our established and effective services. Also, demonstrating the added value of successful early detection (ED) to an existing FES (STEP) in a controlled manner (Secondary Aim) will inform models of how best to resource and implement a comprehensive approach to secondary prevention for psychotic disorders in the U.S. Given this project’s integration within a public-academic collaboration, the results will be primed for national dissemination.

